##### Stretching and Strengthening Control Intervention

This intervention is designed to require a similar amount of physical exertion (stretching and strengthening exercises only, with no extreme movement). Classes will be led by physical therapists or other skilled therapeutic exercise instructors and involve conventional exercises appropriate for patients with CLBP, including a comprehensive set of exercises that stretch all the major muscle groups, with an emphasis on the trunk and legs. The intervention will include 12 stretching exercises used in the exercise arm of previous studies that have successfully compared exercise to yoga [57,58] (ie, gastrocnemius, soleus, quadriceps, posterior and inferior shoulder, upper trapezius, hip flexor, back extension, back rotation, hamstrings, hip external rotators, and back flexion). It will also include 3 additional stretches (hip internal rotators, hip adductors, and hip flexion). Each stretch will be held for approximately 60 seconds and repeated once. In addition to a complete set of full-body stretches, the class will begin with a 5-minute warm up period consisting of basic aerobics steps (ie, 1 minute each of walking in place, marching, lateral shuffling, turning and reaching, and box step) and will also include 4 exercises that strengthen the back, abdomen, and hips (ie, squats, crunches, oblique crunches, and back extensions). Over the 12 weeks, the repetitions of each strength exercise are increased from 8 to 30. Specific strength exercises are practiced in separate sets of 5 to 10 repetitions.

#### Treatment Fidelity

All sessions will be recorded, and instructor fidelity to the yoga intervention or stretching intervention manuals will be evaluated using video-recordings of sessions. Instructors and participants will be aware of and consent to the recordings. We will select 1 session per week from each condition for rating by trained research assistants, who will review sessions using a manual checklist for instructor adherence to the manuals, using a 0-10 rating scale for each procedure or instruction. If the rating is less than 100% adherent, we will meet with the instructor to discuss the places in the session that were not adherent.

### Measures

The assessments of pain intensity, pain interference, ER, and other parameters will be taken at baseline, 6 and 12 weeks, and 3 and 6 months post intervention.

#### Primary Outcome: Primary MOA

Pain severity will be measured with the Brief Pain Inventory-Short Form (BPI-SF) [59] at 12 weeks. The BPI-SF has been validated with CLBP and has shown good reliability [60].

ER as the primary MOA will be measured using the Difficulties in Emotion Regulation Scale (DERS) score at 12 weeks. The DERS is the gold standard self-report measure of individuals’ abilities to respond to emotional experiences in a goal-oriented manner [60]. The 36-item DERS taps aspects of difficulties with ER, which we anticipate will lessen with yoga practice [61]. Participants rate the extent to which each of 36 statements currently applies to them, and the measure yields a total score comprising summed subscales. The DERS is sensitive to change over time in ER, and internal consistency reliability is high [60].

The Negative Affective Priming Task [62] will also be used to capture individual differences in emotional attention, reactivity and appraisal, and ability to inhibit negative emotion and purposefully shift attention to more positive aspects of daily life. Participants are exposed to neutral and affective words with a strong positive and negative valence in consecutive paired trials, one word serving as the “target” and the other as a “distractor.” Participants are instructed to ignore the distractor and to attend to the target in both control and negative priming conditions, with “inhibition ability” operationalized as a difference score between response latencies in control and negative priming conditions. The stronger one’s inhibition abilities, the longer the latency in the negative priming condition compared to the control condition (scored in milliseconds). Individuals with chronic depression and greater tendency to engage in maladaptive rumination demonstrate reduced ability to inhibit negative, as opposed to neutral, words with no difference in the ability to inhibit positive words [63,64].

#### Secondary Outcomes

##### Overview

There are 4 secondary outcomes for this study: pain sensitivity, physical strength and flexibility, pain interference, and quality of life.

##### Pain Sensitivity: Peripheral and Central Sensitivity

We will use a comprehensive quantitative sensory testing (QST) battery of mechanical and thermal stimuli [65]: (1) cutaneous mechanical pain sensitivity, involving measures of tolerance, threshold, temporal summation, and after sensations; (2) heat and cold pain sensitivity, involving threshold, tolerance, and ratings of suprathreshold stimuli; and (3) pressure pain thresholds. Interrater reliability of the QST protocol has been reported in several clinical trials, with each individual test achieving a CI of 0.87-0.94 [66,67].

In addition to the QST battery, we will isolate total RNA from whole blood for sequencing at each time point. We will prepare libraries per Illumina standard protocols and sequence RNA on the Illumina HiSeq2500 System (Illumina Inc) to obtain 150 base pair paired-end reads. We will examine how changes in the expression of pain sensitivity genes, as well as the entire transcriptome, differ between the experimental and control group (those with complete data from yoga vs stretching) × sex using statistical modeling and construct a database of gene expression profiles to generate a profile of change in ER, as well as identify novel therapeutic targets for better pain management. We will use a candidate approach to examine genes identified from our preliminary studies, and a hypothesis-generating approach to identify differentially expressed genes.

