**Methods:**

For this 2-arm parallel group blinded randomized controlled trial, we will enroll 204 adults with CLBP who will be randomized to receive the yoga (n=102) or a control stretching and strengthening (n=102) intervention, which are delivered via web-based synchronous biweekly 75-minute sessions over 12 weeks. Participants are encouraged to practice postures or exercises for 25 minutes on other days using accessible prerecorded practice videos that are sent to participants digitally. Participants will be assessed at 5 time points: baseline, midintervention (6 weeks), postintervention (12 weeks), and 3- and 6-month follow-ups. Assessments of ER, pain severity and interference, pain sensitivity including somatosensory and gene expression profiles, and physical strength and flexibility will be conducted at each visit. The fidelity of the interventions is assessed using a manualized checklist to evaluate recorded group sessions to ensure consistent instructor delivery.

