### Statistical Analysis

The primary aim of this study will test the null hypothesis that the 2 population means are equal between the yoga and stretching and strengthening groups on the primary outcome, pain severity as measured by the BPI-SF, as well as the primary MOA, ER as assessed by the DERS. Power calculations incorporated prior effect sizes from works by others. A proposed sample size of 102 per group, which adjusted for attrition, was calculated to detect statistically significant results with 80% power (estimated *d*=0.50). In consideration of our secondary aims, we also powered the detection of paths a and b within pain interference mediation models. This was done using simulation in R (R Foundation for Statistical Computing; N=5000). Following simulation methods (N=5000) presented in Fritz and MacKinnon [76], sample size was determined by increasing simulation sample size until 90% of simulations significantly detected both paths a and b with estimated effect size magnitudes of *d*=0.39 (path a) and *d*=0.26 (path b) at α=.05. A proposed sample size of 116 was calculated, which was already reached when powering our primary aim.

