### Data Analysis

All analyses will be performed in SPSS (version 29; IBM Corp). A *P* value of .05 or less will be considered statistically significant. The primary outcome is pain severity (BPI-SF) and the primary MOA is ER (DERS). We will examine baseline demographics and study variables descriptively and test for differences between yoga and stretching and strengthening groups. If assumptions are met, a series of 2-sided *t* tests, mixed effects models, and path analyses will test our hypotheses. A mediation path analysis will be conducted examining the indirect path of group and change in ER from baseline to 6 weeks (path a), and change in ER from baseline to 6 weeks and pain severity (BPI-SF) at 12 weeks (path b) controlling for baseline pain severity. The magnitude of indirect path b will be assessed controlling for path a and the direct path between group and change in pain severity at 12 weeks (path c) to test if changes in ER predict subsequent changes in pain severity. Identical models will be created with change in ER from baseline to 12 weeks and pain severity at 3- and 6-month follow-ups. The magnitude of indirect path b will be compared between groups to test if the path between ER and pain severity is greater in the yoga group than in the stretching and strengthening group. If 95% CIs of path estimates do not contain 0, they will be considered meaningful. Finally, a series of moderated mediation path analyses will be conducted, examining the measures of baseline pain sensitivity (QST scores and normalized gene expression values), strength and flexibility, pain interference, and quality of life as moderators of the identical mediation model. All analyses will also be adjusted for important covariates including, but not limited to demographics (eg, biological sex, race, and sex), cohort, instructor, and intervention components (Essential Properties of Yoga Questionnaire) and credibility or perception of success (Credibility Expectancy Questionnaire). Sensitivity analyses will examine whether treatment responders and nonresponders differ significantly in baseline ER abilities. Baseline DERS scores will also be examined as a continuous moderator in main study analyses to establish whether some individuals may enjoy greater benefit from this intervention more than others.

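### The between-arm comparison of change in gene expression is restricted to an undefined set with complete data, so it compares completers and not the groups as randomised

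*Protocol article*

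**What the plan says.** The restriction stands in the protocol article under Pain Sensitivity: Peripheral and Central Sensitivity. Changes in expression, for pain sensitivity genes and for the whole transcriptome, are to be examined for how they "differ between the experimental and control group (those with complete data from yoga vs stretching"), crossed with sex. The same paragraph says that "we will isolate total RNA from whole blood for sequencing at each time point". The Abstract sets the schedule: "Participants will be assessed at 5 time points: baseline, midintervention (6 weeks), postintervention (12 weeks), and 3- and 6-month follow-ups".

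On the status of the outcome, the Secondary Outcomes overview states: "There are 4 secondary outcomes for this study: pain sensitivity, physical strength and flexibility, pain interference, and quality of life". The Abstract counts gene expression within that outcome, as "pain sensitivity including somatosensory and gene expression profiles".

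Dropout is expected. Under Statistical Analysis: "A proposed sample size of 102 per group, which adjusted for attrition, was calculated to detect statistically significant results with 80% power", for an effect size of 0.50. No attrition rate is given. Ethical Considerations allows withdrawal at any time.

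No other section widens the gene-expression comparison. Data Analysis lists t tests and then "mixed effects models, and path analyses will test our hypotheses", without assigning a model to expression. The pain sensitivity section speaks only of statistical modelling.

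**The concern.** Whether a participant has complete data is known only after randomisation. It depends on staying in the study, attending visits and giving usable samples. Both programmes ask for two 75-minute classes a week plus home practice, and staying can plausibly depend on the course of pain or on how well the assigned programme suits the participant. If those influences differ between arms, the completers in the two arms are no longer comparable, and a difference in expression change may reflect who stayed.

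There may also be a loss of precision. With five scheduled samples, a participant may hold a baseline and a 12-week sample but lack a later one. If complete means the full series, those two usable samples are dropped from the 12-week comparison.

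The parenthesis is a stated choice of analysis set, so this is not a detail that the article merely leaves to a fuller document. What the article does leave open is the meaning of complete, and the size of the problem turns on that.

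**Working it through.** **1. The plan's own sample size, used only to find an attrition scenario.** Inputs: effect size 0.50 and 80% power (Statistical Analysis); two-sided tests at 0.05 (Data Analysis).

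- Normal approximation: n = 2 × (1.960 + 0.842)² / 0.50² = 62.8, so 63 per arm. The t test needs 64.
- The stated 102 is adjusted for an unstated attrition rate, so it can be neither confirmed nor refuted. The rate that would connect the two figures is 1 − 64/102 = 0.373. At 20% loss the result would be 64/0.80 = 80.

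I therefore use 20% and 37% as assumed scenarios. Neither is a figure of the protocol. Placing the loss at the 6-month follow-up is a further assumption, because the sample size concerns the primary aim at 12 weeks.

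**2. Precision if complete means all five samples.** Assume that everyone has a baseline sample and that a constant fraction r is retained at each of the four follow-ups. Final retention is r⁴. The 12-week visit is the second follow-up, so r² have a 12-week sample. The standard error varies as 1/√n, so the ratio is √(r²/r⁴).

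| Final loss (assumed) | Complete, r⁴ | With 12-week sample, r² | SE ratio |
|---|---|---|---|
| 20% | 0.80 | 0.894 | √(0.894/0.80) = 1.06 |
| 37% | 0.627 | 0.792 | √(0.792/0.627) = 1.12 |

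Per arm of 102 this is about 82 against 91 at 20% loss, and 64 against 81 at 37%.

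A different pattern gives a figure of the same order. If each draw is missed independently 10% of the time, 0.9⁵ = 59% have all five samples and 0.9² = 81% have both baseline and 12 weeks. The ratio is √(0.81/0.59) = 1.17.

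**3. Precision if complete means a baseline and follow-up pair.** The 12-week comparison then already uses everyone with both samples, and the ratio is close to 1. A longitudinal model would add only the partial information from participants who lack one of the two.

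**4. Bias, under either reading.** Its size cannot be derived from the article. As an illustration, assume no true difference, a change score with SD 1, and exclusion in one arm only, with log-odds rising by 0.25 to 1.0 per SD of change. The spurious difference among completers is about 0.05 to 0.17 SD when 20% are excluded and 0.09 to 0.31 SD when 37% are. In this scenario exclusion depends on the change itself, so a mixed model would remove only the part that earlier observed samples predict.

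**The case against.** The strongest reply is that the parenthesis says less than a reader may infer from it. Most of this stands.

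- **One missed draw removes all of a participant's samples.** The article does not say this. Complete could mean all five visits, the pair needed for a change score, or all measures. The 6% and 12% hold only for the first reading.
- **The whole pain sensitivity outcome or the sensitization hypothesis is compromised.** The wording covers expression change only, not quantitative sensory testing. Data Analysis tests moderation with baseline sensory scores and baseline expression. Part of the expression work is expressly hypothesis-generating, although the candidate-gene comparison of arms does serve the secondary outcome.
- **A completers' analysis is valid only if data are missing completely at random.** This is too strong. An adjusted complete-case analysis is also valid when missingness is unrelated to the outcome given the covariates in the model, and Data Analysis plans covariate adjustment. The weakness appears when missingness depends on earlier expression, pain or adherence that the model omits.
- **The protocol expects 37% attrition, or the samples are already in hand.** It gives no rate, and 138 of 204 participants had been enrolled by January 2024.
- **Mixed models are already planned for expression.** They appear only in a general list.

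None of this changes the central fact: the article restricts the set to those with complete data, and no section widens it. Under the mildest reading the comparison is still of completers.

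**Conclusion.** The concern holds in a limited form. For the between-arm comparison of change in gene expression, the article fixes a completers-only set that is determined after randomisation and not defined. On every reading this leaves the comparison open to dropout bias, of a size that the article does not allow one to compute.

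A loss of usable samples follows only if complete means the full series. Under steady attrition that I have assumed, it enlarges the 12-week standard error by about 6% at 20% final loss and about 12% at 37%. If a baseline and follow-up pair is meant, the loss is small.

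The point should be corrected because it touches a named secondary outcome in a trial that expects attrition. It does not bear on the primary outcome, on sensory testing or on the baseline-moderator analyses.

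**What to change.** Delete the parenthesis. State that arms will be compared, as randomised, in all randomised participants with at least one usable RNA sample, using a longitudinal mixed-effects model with group, time, sex and their interactions and a participant random effect. Keep a complete-data analysis as a sensitivity analysis, and define complete there.

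Such a model relies on missingness being explained by the data it contains: observed expression, arm and sex. If dropout is thought to follow pain or adherence, the plan should say how those measures will inform the handling of missing samples.

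The cost is small: a change to the analysis wording and a somewhat more complex expression model. All planned samples must be sequenced, including those from incomplete series, which the pain sensitivity section already provides for. No interim analyses are planned and analysis follows final data collection, so the change can be made before results are known.

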##### Physical Strength and Flexibility

Physical measures include grip strength and core stabilization and strength. Grip strength will be measured using 2 trials for each hand with a hydraulic dynamometer. The best performance is selected for each side, and the average of the left and right hand is used for analysis. Painful or injured hands or wrists are not tested, and the result of the good hand is used. Good reliability and predictive validity have been shown [68]. Core stabilization and strength will be assessed using prone and supine bridge positions [69]. Participants begin on their elbows in the prone position with shoulders, hips, and ankles aligned. The supine position is tested next, with knees flexed 90° and pelvis raised from the floor with shoulders, hips, and knees aligned. Assessors record the length of time (120 seconds maximum) that each position is held in proper form.

##### Pain Interference

Interference of function due to pain will be measured with the Brief Pain Inventory [60]. The pain interference score is the mean of the 7 interference items.

##### Quality of Life

The 36-item Short Form Health Survey [70] will be administered at each time point to gain a deeper understanding of the psychological, physical, and social limitations that participants experience as a result of pain. Subscales characterize participants’ physical functioning, role functioning as impacted by physical and emotional health, energy or fatigue, emotional well-being, social functioning, pain, and general health. The 36-item Short Form Health Survey demonstrates excellent strong psychometric properties and predictive validity in a variety of diverse samples, including those experiencing chronic pain [71].

### Exploratory Variables

Demographics, class attendance or home practice, expectancies, and substance use will be measured to examine the impact on the primary and secondary outcomes. A brief questionnaire (minimum data set as recommended by the National Institutes of Health Taskforce on Research Standards for CLBP) [54] will assess demographics (age, gender, race or ethnicity, education, and employment status) and medical or psychiatric history (comorbidities, medication usage, and ongoing treatments). Attendance at yoga or stretching sessions will be assessed using attendance data from the session recordings. The Essential Properties of Yoga Questionnaire [72] will be used to rate both interventions (yoga and stretching or strengthening) and measures the extent to which 14 different dimensions are emphasized in a mind-body intervention (eg, physical challenge, breathwork, restorative postures, and mindfulness). The Credibility Expectancy Questionnaire [73], a 6-item self-report instrument, will be used to assess treatment credibility and patient expectancy for improvement [74]. In order to assess participants’ use of tobacco, alcohol, prescription medicines, cannabis, and other nonprescribed substances, the Alcohol, Smoking, and Substance Involvement Screening Test [75] will be administered by study staff at each time point.

### Statistical Analysis

The primary aim of this study will test the null hypothesis that the 2 population means are equal between the yoga and stretching and strengthening groups on the primary outcome, pain severity as measured by the BPI-SF, as well as the primary MOA, ER as assessed by the DERS. Power calculations incorporated prior effect sizes from works by others. A proposed sample size of 102 per group, which adjusted for attrition, was calculated to detect statistically significant results with 80% power (estimated *d*=0.50). In consideration of our secondary aims, we also powered the detection of paths a and b within pain interference mediation models. This was done using simulation in R (R Foundation for Statistical Computing; N=5000). Following simulation methods (N=5000) presented in Fritz and MacKinnon [76], sample size was determined by increasing simulation sample size until 90% of simulations significantly detected both paths a and b with estimated effect size magnitudes of *d*=0.39 (path a) and *d*=0.26 (path b) at α=.05. A proposed sample size of 116 was calculated, which was already reached when powering our primary aim.

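### Two unreconciled planning values, d=0.50 and d=0.39, are given for the arm effect on emotion regulation; if 0.39 is a between-arm d as labelled, the 80% figure does not extend to DERS after attrition and the 90% mediation power is not met at 204

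*Protocol article*

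**What the plan says.** All the power statements are in one paragraph of the protocol article, Methods, Statistical Analysis.

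- **Primary aim.** The null hypothesis is equality of the two arm means on BPI-SF pain severity "as well as the primary MOA, ER as assessed by the DERS". One effect size is given for this aim: the planned number "was calculated to detect statistically significant results with 80% power (estimated *d*=0.50"). The number itself is described as "A proposed sample size of 102 per group, which adjusted for attrition"; no rate is given.
- **Secondary aims.** Paths a and b of mediation models for pain interference were powered by simulation until 90% of runs detected both, with d=0.39 for path a and d=0.26 for path b at α=.05. The result was 116, which the paragraph says the primary-aim sample size had already covered.

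The Data Analysis section defines the first mediation link as "the indirect path of group and change in ER from baseline to 6 weeks (path a"). It adds identical models that use the ER change to 12 weeks. The Measures section sets the primary mechanism as DERS at 12 weeks. The significance threshold is a P "value of .05 or less will be considered statistically significant", and the t tests are two-sided.

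**The concern.** Path a runs from randomised group to the mediator. It does not involve the outcome, so it is the arm difference in ER whether the outcome is pain severity or pain interference. The primary aim also tests the arm difference in ER. The paragraph plans this effect at 0.50 in one sentence and 0.39 in another, and gives no reason such as a different visit or a different scale.

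This matters because the trial is built around a mechanism. If the arm effect on ER is not detected, the mediation question has no first link. A reader is told that the aim containing the DERS contrast has 80% power, and that 90% power for both mediation paths comes with it. If the expected ER effect is really d=0.39, both statements are too favourable for ER, and a null DERS result could be given more weight than the design supports.

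**Working it through.** **Inputs.** From Statistical Analysis: d=0.50, 80% power, 102 per group after allowing for attrition, path a d=0.39, path b d=0.26, 90% for both paths, N=116. From Data Analysis: two-sided tests at α=0.05. Attrition is not given, so the losses below are assumptions.

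**Step 1: the plan's own 80% figure.** Normal approximation: n per arm = 2(1.960+0.842)²/d².

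- d=0.50: 2 × 7.85 / 0.25 = 62.8, so 63; the noncentral t gives 63.8, so 64.
- With 64 evaluable per arm, 80% at d=0.50 holds. Going from 64 to 102 implies a loss of 1 − 64/102 = 37%. The article does not state this rate, and other unstated inputs could also lead to 102.
- With all 102 per arm analysed, power at d=0.50 is 94.5%.

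**Step 2: the same test at d=0.39.** Required n: 2 × 7.85 / 0.1521 = 103.2, so 104; the noncentral t gives 104.2, so 105. Power ≈ Φ(d√(n/2) − 1.96); for n=102 this is Φ(0.39 × 7.141 − 1.96) = Φ(0.825) = 79.5%. Noncentral-t results:

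| Evaluable per arm | Assumed loss | Power at d=0.39 |
|---|---|---|
| 102 | none | 79% |
| 92 | 10% | 75% |
| 82 | 20% | 70% |
| 64 | 37% | 59% |

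**Step 3: the 90% mediation statement, with 0.39 read as a between-arm d.** The power to detect both paths cannot exceed the power for path a alone. That is at most 79% with all 204 analysed, so 90% for both is out of reach at 204. A simulation of joint significance (3,000 runs, residual variances of 1, 0.26 as the coefficient for path b, no direct effect) gives about 75% for both paths at 204 and 43% at 116. About 290 to 300 in total are needed for 90%.

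**Step 4: 0.39 read as a standardised coefficient.** For a balanced binary group the equivalent is d = 2 × 0.39 / √(1 − 0.39²) = 0.78 / 0.921 = 0.85. That is larger than 0.50, so the DERS contrast has no shortfall. The same simulation with 0.39 and 0.26 as coefficients on a unit-variance predictor gives about 95% for both paths at 204. At 116 it gives about 76%, and about 160 are needed for 90%.

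**Step 5: do the plan's numbers settle the scale?** No. N=116 gives 43% on the first reading and 76% on the second, against a stated 90%. The second is nearer, but neither reproduces it.

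**The case against.** A reader might infer that the article contradicts itself outright and that its 80% power claim is wrong. The documents do not support that, for four reasons.

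- **Not certainly the same effect.** Path a is first defined on the 6-week change, midway through the intervention, in models serving secondary aims. The primary mechanism is DERS at 12 weeks. A smaller mid-course effect would not be a contradiction. This stands as a possible explanation. It is not a stated one: the identical models use the 12-week change, and 0.39 is tied to no visit.
- **No real shortfall without attrition.** At 102 per arm, 79% is effectively 80%; the detectable d at 80% power is 0.394. Any material loss of power depends on attrition that the article does not quantify. This stands. Because the 102 is said to include attrition already, fewer than 102 evaluable are expected, but the 70% and 59% figures are conditional.
- **The direction may reverse.** If 0.39 is a coefficient, the implied d of about 0.85 gives DERS more than enough power. The failure of 116 to reproduce with 0.39 as a between-arm d makes this reading plausible. This stands too, and it means the label d is then the error.
- **The source may be in the full protocol.** The article says the effect sizes came from earlier work, and their derivation may be given elsewhere. That could explain the two values, but both are printed here without a distinction, and the power statements are built on them.

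**Conclusion.** The point holds in a limited form. The Statistical Analysis section uses two planning values for the arm effect on ER and does not reconcile them. The 80% statement is correct at d=0.50 with 64 evaluable per arm, and nothing here challenges it for BPI-SF severity.

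Two readings remain, and each leaves something to correct:

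1. **0.39 is a between-arm d, as labelled.** The 80% figure does not carry over to DERS at that value after attrition (75% to 59% for assumed losses of 10% to 37%). The statement that the 90% requirement for paths a and b was covered by the primary-aim sample size fails, because path a alone has at most 79% power at 204. This second conclusion needs no attrition assumption.
2. **0.39 is a standardised path coefficient.** The label is wrong and DERS has no shortfall, but its implied d of about 0.85 still does not agree with 0.50.

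Applying the 0.39 calculations to the primary mechanism also assumes that the value is meant for the 12-week contrast.

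**What to change.** In the Statistical Analysis paragraph:

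- State whether the path-a and path-b values are between-arm d or standardised coefficients, and which visit the path-a value refers to. If 0.50 and 0.39 differ because one is for 12 weeks and the other for 6, say so.
- Give one justified effect for the 12-week DERS contrast.
- Limit the 80% statement to the outcome and effect it covers, for example BPI-SF severity at d=0.50.
- State the assumed attrition, and restate the power for DERS and for paths a and b at 204 after that loss. Report about 79% with no loss and 70% at 20% loss for DERS only if 0.39 is confirmed as a between-arm d; if it is a coefficient, those figures would be wrong.

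The cost is rewording and a short recalculation. Sample size and conduct do not change. The downside is that the stated power for the mechanism may become less favourable.
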